### Sample size

The sample size was calculated primarily to detect clinically relevant differences in radiological progression of the affected joints between the two groups (treatment and placebo) after two years of follow up. To detect a difference of 0.25 mm in radiological progression (SD 0.5) between the intervention and placebo groups (power 80%, alpha 5%, one-tailed testing) after two years of follow-up, 63 patients with hip osteoarthritis are needed per group. These calculations are based on an average change of 0.33 mm in joint space (SD 0.5) during one year of follow-up of patients with hip osteoarthritis [12].

Fewer patients are needed to detect relevant clinical differences: to detect a difference of 25% in pain (Western Ontario McMaster Universities Osteoarthritis index (WOMAC)) with one-tailed testing, a power of 80%, and alpha 5% (Mean 4.83, SD 2.25 [13]) 55 patients per group are needed. To detect the same difference in function (WOMAC) (mean 4.81, SD 2.18 [13]) 51 patients are needed per group.

As we expect a 20% loss to follow-up, we need to include 150 patients. However, to create options for studying effect-modification by type and severity of osteoarthritis, we oversized this trial to 220 patients (110 in each group).

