### Current status

A total of 40 GP's were found willing to participate in the study. They sent a total of 600 letters to inform possible eligible patients of the study. We received 417 requests for additional information and thus sent an equal amount of information folders. Of these 417 people 250 returned a written informed consent. Eventually 222 people entered the study. Of the 28 people that did not enter the study, most did not meet the inclusion criteria and a few people changed their mind and withdrew their informed consent before randomisation.

We started including patients at the end of September 2003 and the last patient was included on March 15^th ^of 2004. This means the study will run until March 2006. The first results will be available around September 2006.

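### The stated requirement of 150 patients does not follow from 63 per group with 20% loss (158 needed), and the 63 is a two-sided size labelled one-tailed

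*Protocol article*

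**What the plan says.** All the inputs are in the Sample size section of the protocol article.

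- **Target:** "To detect a difference of 0.25 mm in radiological progression (SD 0.5) between the intervention and placebo groups".
- **Error rates:** "power 80%, alpha 5%, one-tailed testing".
- **Resulting size:** "after two years of follow-up, 63 patients with hip osteoarthritis are needed per group". The 63 is therefore the number wanted at the end of follow-up, before any allowance for loss.
- **WOMAC outcomes, also described as one-tailed with 80% power and alpha 5%:** a 25% difference in pain (mean 4.83, SD 2.25) is said to need 55 per group. The same relative difference in function (mean 4.81, SD 2.18) is said to need 51.
- **Allowance for loss:** "As we expect a 20% loss to follow-up, we need to include 150 patients".

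The next sentence raises the target to 220, or 110 per group, so that effect modification by type and severity of osteoarthritis can be studied. The Current status section reports the final intake: "Eventually 222 people entered the study".

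**The concern.** A reader should be able to get from 63 per group and 20% expected loss to the stated total. Here the total comes out too small: 20% of 150 is 30, which leaves 120 patients, or 60 per group, against the 63 that the same paragraph asks for.

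Checking where the 63 comes from shows a second mismatch. The section names a one-tailed test, but the per-group sizes look like two-sided ones. The two problems are linked, because the right replacement for 150 depends on which sidedness the plan means. What is at stake is whether the published sample-size justification can be reproduced and whether the test it describes is the one it was computed for.

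**Working it through.** **Inputs** (Sample size section): difference 0.25 mm, SD 0.5, so a standardised difference of 0.5; alpha 5%; power 80%; equal groups; 20% loss. The normal-approximation formula is n per group = 2(z_alpha + z_beta)² / d², with z_beta = 0.842, and z_alpha = 1.960 two-sided or 1.645 one-tailed.

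**Step 1: reproduce the 63.**
- Two-sided: 2(1.960 + 0.842)² / 0.25 = 62.8, so 63. This matches the protocol.
- One-tailed: 2(1.645 + 0.842)² / 0.25 = 49.5, so 50. This does not match.
- Using the t distribution gives 63.8 two-sided and 50.2 one-tailed, which leads to the same conclusion.

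**Step 2: check the WOMAC sizes the same way.**

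| Outcome | Standardised difference | Stated | Two-sided | One-tailed |
|---|---|---|---|---|
| Pain | 0.25 × 4.83 / 2.25 = 0.537 | 55 | 55 | 43 |
| Function | 0.25 × 4.81 / 2.18 = 0.552 | 51 | 52 (51.6 before rounding up) | 41 |

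All three stated sizes agree with a two-sided 5% test, to within one patient for function. None agrees with a one-tailed test.

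**Step 3: allow for 20% loss.** The total to include is the number needed divided by (1 − loss).
- From the stated 63: 2 × 63 = 126, and 126 / 0.8 = 157.5, so 158. Per group, 63 / 0.8 = 78.75, so 79.
- From a one-tailed size of 50 or 51: 100 / 0.8 = 125, and 102 / 0.8 = 127.5, so 128.
- From the pain outcome's 55: 110 / 0.8 = 137.5, so 138.
- Multiplying instead of dividing: 126 × 1.2 = 151.2. This is near 150 and may be its origin, but the document does not say so. It is also not the operation that leaves 126 after 20% loss.

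No correct route gives 150. In the other direction, 150 × 0.8 = 120, or 60 per group, and 150 retains 126 only if loss is at most 1 − 126/150 = 16%.

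**Step 4: what this means for power** (d = 0.5, alpha 5%, 20% loss, normal approximation). Power is Φ(d√(n/2) − z_alpha). For n = 60, d√(n/2) = 2.739, giving Φ(2.739 − 1.645) = 86.3% one-tailed and Φ(2.739 − 1.960) = 78.2% two-sided.

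| Included | Left per group | One-tailed | Two-sided |
|---|---|---|---|
| 150 | 60 | 86.3% | 78.2% |
| 158 | 63.2 | 87.8% | 80.3% |
| 220 | 88 | 95.3% | 91.3% |
| 222 | 88.8 | 95.4% | 91.5% |

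The t distribution lowers these by less than one percentage point (77.5% for 150 two-sided, 91.0% for 220 two-sided).

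**The case against.** The strongest reply is that the figure had no consequence. The 150 was an intermediate number, replaced in the next sentence by 220, and 222 patients entered. It governed neither recruitment nor analysis. This stands, and it is why the point is minor.

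A second reply concerns power. A reader might infer that 150 patients would not deliver the stated power. The documents do not support that. The section attaches its 80% to a one-tailed test, and under that test 60 per group gives about 86%, which exceeds the target. A shortfall appears only on the two-sided basis that reproduces the 63, and even there it is about 2 percentage points. This reply also stands. What remains is narrower: 150 does not deliver the 63 per group that the section says are needed.

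A reader might also infer that the room for studying effect modification is overstated, since 220 exceeds 158 by 62 rather than exceeding 150 by 70. The section claims no numerical surplus, no interaction power and no subgroup size, so nothing stated in the plan rests on that subtraction.

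Finally, 158 can be called the right total only if 63 is kept. Under the one-tailed test as written, 125 to 128 would be enough. This stands too, and it is why the total cannot be corrected without settling the sidedness.

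**Conclusion.** The point holds as an error in stated figures. Given 63 per group and 20% loss, the total should be 158, so 150 is 8 short. Separately, the one-tailed description and the per-group sizes contradict each other: 63, 55 and 51 are two-sided sizes, and the one-tailed equivalents are about 50, 43 and 41.

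The main comparison is not endangered. With the planned 220 and 20% loss, power for 0.25 mm is about 91% two-sided or 95% one-tailed. These figures rest on the section's own difference and SD, equal allocation, loss spread evenly over the groups, and an unadjusted comparison of two means.

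**What to change.** Reconcile the sidedness first, then restate the total to match.

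- **If 63 per group is kept:** describe the test as two-sided 5% throughout the Sample size section and change 150 to 158 (79 per group). The 55 for pain then stands, and the 51 for function becomes 52 if rounded up.
- **If one-tailed testing is kept:** restate the per-group sizes as about 50, 43 and 41, and the total after 20% loss as 125 to 128, depending on rounding and on whether the normal or t calculation is used.

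Stating the inflation formula (number needed divided by 0.8) would let a reader verify the total. Giving the power at the enrolled 222 would be helpful but is optional.

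The cost is a few words and figures. No further patients are needed, because 222 have already entered, and the planned between-group comparison is unchanged apart from the need to state its sidedness consistently.

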### Intervention

Patients who participate in the trial are randomised to either GS or a placebo for the duration of two years. To ensure a daily intake of 1500 mg GS, they are required to take two pills each day. The GS and placebo pills are identical in taste and appearance and were delivered in identical plastic bottles. This will ensure true blinding of the patients and of the researchers. Blinding of the patients will be tested after two years; if people can guess what sort of pills they were taking, this might have an influence on the subjective measures. This will therefore be taken into account in the analysis of the data.

The Department of Nutritional Sciences at Numico Research BV manufactured the pills used in this trial.

### Randomisation

Following informed consent and baseline assessments, patients are allocated to the intervention or control group using a blinded randomisation list. The randomisation list contains four different strata and is randomised per block of six numbers. This list was generated with a computer by an independent researcher. This researcher also handled labelling the pill-bottles with the randomisation numbers. The researchers involved in this project received all bottles after they were labelled, ensuring blinding to treatment allocation. The randomisation list with the key to treatment allocation will be kept in a safe until the end of the trial. To be able to perform the analyses blinded, the allocation to treatment A and treatment B will be provided, but not the key to A and B.

People are assigned to one of the four different strata on the basis of the Kellgren-Lawrence score of the hips, knees and hands. A researcher ([name]) will score all the radiographs according to the Kellgren-Lawrence score. The outline of the four different strata is given in table 1. Once the correct stratum is established at baseline, the patient is given the subsequent unique four-digit randomisation number from his/her stratum on the randomisation list. This number is used for labelling study materials and data. By stratifying, patients are optimally distributed to GS and placebo in the different strata, which makes comparing people with mild OA to people with moderate-severe OA, and comparing people with local OA to people with generalised OA possible. In this way, we will be able to study whether effect of treatment depends on severity or localisation of OA.

**Table 1 T1:** Outline of the randomisation strata

	**Hip radiograph**	**Knee and hand radiographs**	**Type**
**Group 1**	K-L score < 2	K-L score < 2 for hands and knees	mild + localised
**Group 2**	K-L score < 2	K-L score ≥ 2 for hands and/or knees	mild + generalised
**Group 3**	K-L score ≥ 2	K-L score < 2 for hands and knees	moderate/severe + localised
**Group 4**	K-L score ≥ 2	K-L score ≥ 2 for hands and/or knees	moderate/severe + generalised

### Measurements

Data for the primary and secondary outcome measures are being collected at different time-points throughout the trial. An overview of the timing of the measurements and the outline of the primary and secondary outcome measures is given in table 2.

**Table 2 T2:** Timing of measurements and outline of primary and secondary outcome measures

	**0 m** B.A.	**3 m** Q	**6 m** Visit	**9 m** Q	**12 m** Visit	**15 m** Q	**18 m** Visit	**21 m** Q	**24 m** F.A.
**Primary outcome measures**									
Joint space width	**x**								**x**
Pain score (WOMAC)	**x**								**x**
Function score (WOMAC)	**x**								**x**
									
**Secondary outcome measures**									
Subchondral bone quality	**x**								**x**
Stiffness score (WOMAC)	**x**	**x**	**x**	**x**	**x**	**x**	**x**	**x**	**x**
Quality of life (EuroQol EQ-5D)	**x**	**x**	**x**	**x**	**x**	**x**	**x**	**x**	**x**
Medical consumption	**x**	**x**	**x**	**x**	**x**	**x**	**x**	**x**	**x**
Side effects		**x**	**x**	**x**	**x**	**x**	**x**	**x**	**x**
CTX-II	**x**		**x**		**x**		**x**		**x**
									
**Possible confounders/Effect modifiers**									
Type of OA (localised – generalised)	**x**								
Radiological severity	**x**								**x**
Joint function	**x**								**x**
Age	**x**								
Gender	**x**								
Activity level	**x**	**x**	**x**	**x**	**x**	**x**	**x**	**x**	**x**
Co-interventions	**x**	**x**	**x**	**x**	**x**	**x**	**x**	**x**	**x**
Compliance (BMQ)		**x**	**x**	**x**	**x**	**x**	**x**	**x**	**x**
Compliance (pill count)			**x**		**x**		**x**		**x**

Note: 0 m: 0 month of follow up, 3 m: 3 months of follow up etc. B.A.: baseline assessment. Visit: 6 monthly visit. F.A.: final assessment

In brief, the trial starts for every patient with a baseline assessment at the research centre. At the end of this assessment, patients receive a supply of GS or placebo sufficient for seven months. After the baseline assessment, patients will receive a questionnaire every three months, which has to be returned to the researchers, except from those at 6, 12 and 18 months after baseline, which will be collected by the researchers during a home visit. After two years, patients return to the research centre for the final assessment, which marks the end of the trial. The collection of the outcome measures is described in the following sections.

#### Radiographs

Radiographs are taken during the baseline assessment and during the final assessment two years later.

At baseline, three anteroposterior (AP) radiographs are taken, one of the pelvis, one of both knees, and one of both hands. All radiographs are used to establish what stratum the subject belongs to (table 1). The radiographs of hands and knees will not be used to determine outcome measures and will therefore not be repeated at follow up. As follows from table 1, people with knee and/or hand OA are stratified to one of the 'generalised OA' groups (2 or 4).

A highly standardised protocol is used to make the weight-bearing, AP pelvic radiographs at baseline and follow-up, allowing for a correct measurement of our primary outcome variable: joint space narrowing. The patients' feet are positioned alongside a frame, which was designed to ensure 15° internal rotation of the hips. A second frame (no internal rotation) is available for patients with severe mobility restrictions of the hips. The frame used during the baseline radiograph of a patient will also be used two years later for his/her follow up radiograph. Patients are asked to stand upright. If present, flexion in hips or knees is recorded. Protocol for the pelvic X-ray further states that focus-to-film distance should be 130 cm and that the X-ray beam should be centred on the superior aspect of the pubic symphysis. The X-rays are digitised.

The X-rays from baseline and final assessment will be analysed side by side. The minimal joint space width (JSW) will be identified from the baseline X-ray by assessing four different points: medial, axial, superior and lateral [14]). The researcher will also identify a point that appears to be the minimal JSW. From these five points the actual minimal JSW will be determined. This point will be used to measure changes in joint space width over the two-year follow up period.

#### Dexa-scan

During the baseline and final assessment, a Dual Energy X-ray Absorptiometry (DEXA) scan will be used to make scans of the pelvis. A frame similar to the one used for the radiograph of the hips is also used to make the DEXA-scan, ensuring 15° internal rotation of the hips. The scan will be used to study quantitative changes in subchondral bone density both of the affected joint and of the contra-lateral joint. Subchondral bone-density alterations might indicate osteoarthritic progression. This long-term trial can be helpful to determine whether pre-clinical OA can be recognised from a DEXA-scan. And, if so, whether GS prevents the onset or progression of OA in the pre-clinical stage.

#### Physical examination

A physical examination is carried out at baseline and is repeated during the final assessment. At baseline, this test is first of all used to check part of the inclusion criteria. Various tests are also carried out to check for co-existing musculoskeletal disorders. Findings from the physical examination will be used as baseline characteristics, and to register clinical signs and joint function after two years of follow up. Joint function is established by assessing pain due to joint motion, and by measuring limitation of joint motion with a two-arm goniometer.

#### Questionnaires

Throughout the study, patients will fill out a total of nine questionnaires. The first during the baseline assessment, followed by a questionnaire every three months in the following two years (including the last one during the final assessment).

The baseline questionnaire is used to measure different patient characteristics (age, gender, race, social status, Body Mass Index (BMI)), disease related characteristics (localisation of symptoms, duration of symptoms, family history) and co-morbidities. Of these characteristics, BMI and co-morbidities will be monitored throughout the trial.

Three validated instruments are used in all nine questionnaires: the WOMAC questionnaire will be used to establish severity of clinical status. It contains subscales for pain, stiffness and function. The WOMAC questionnaire is extensively validated and recommended for clinical assessment in osteoarthritis trials by the WHO [15]. The EuroQol (EQ-5D) will be used to measure quality of life, because of the usefulness of this scale in cost-effectiveness analysis [16,17]. The cost-effectiveness analysis will also be based on employment status, sick leave, changes in work-tasks or other work-related adjustments, and on medical consumption. The SQUASH questionnaire is used to measure load level in work and sports [18].

In the eight follow-up questionnaires, patients will be asked to answer questions about alterations in their symptoms (i.e. whether they improved or deteriorated), which will be measured with a 7-point Likert scale. Also, compliance to treatment is measured with the Brief Medication Questionnaire (BMQ) [19].

#### Laboratory assessments

At baseline, two samples of blood are collected. The first to measure the erythrocyte sedimentation rate (ESR), which is used for the inclusion criteria (ACR-criteria). The second sample is stored at -20°C to create options for future DNA-research, for which patients gave separate written informed consent.

Throughout the study, we will collect samples of second-morning void urine of all patients. In urine a marker of cartilage degradation can be found, called CTX-II. In the Rotterdam study [20] this marker was found to be predictive of radiological progression of hip and knee OA. It may therefore be used to assess the effect of treatment on the progression of OA. Urine samples will be collected at baseline and once every six months during follow up. At the end of the study a total of five samples will be available from every patient. These urine samples are stored at -80°C. If promising new markers are discovered during the course of the study, these can also be included in the analysis.

### Half-yearly visits

Every six months one of the researchers will visit the patients at home. The main reason for this visit is to provide the patient with new pills (sufficient for seven months). To be able to calculate compliance to treatment, the pills remaining of the previous supply will be collected. The amount of remaining pills combined with the score on the compliance questionnaire (BMQ) will give a good indication of the actual amount of pills the patient has been taking. Finally, a sample of second-morning void urine on the day of the visit will be collected.

### Analyses

The researchers will be aware of allocation to treatment A or B at the time of the statistical analyses, but will not know which group received GS and which group received the placebo. All analyses will take place after the trial has finished, no intermediate analyses will be performed.

Success of randomisation and normality of outcome measures will be checked before actual analyses are done. Differences in the primary outcome measures JSN and WOMAC (pain and function) between the intervention and placebo group will be analysed on the basis of the 'intention to treat' principle using linear regression models. Additionally a per-protocol analysis will be done. When it turns out that randomisation was (partially) unsuccessful, we will adjust for differences in prognosis. Using baseline characteristics, we can identify factors that influence outcome of the study. Factors that change the outcome with 10% will be regarded as confounders and will therefore be added to the regression-model.

A cost-effectiveness analysis will be performed from a social and a patient perspective, looking at differences in direct and indirect health care cost between the two groups (GS and placebo). If the trial does not show a difference in disease parameters (WOMAC) and quality of life (EuroQol) between the GS and the placebo group, the analysis will be reduced to a cost minimisation analysis. This form of analysis evaluates the efficacy of treatment based solely on direct and indirect costs. If the study does find a positive difference in disease parameter and/or quality of life a cost-effectiveness ratio can be determined with on the one hand the costs and savings and on the other hand the disease-specific parameters and also quality of life.

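### The primary regression has no fixed covariate set: an undefined check of randomisation and a 10% change rule decide it from the trial data

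*Protocol article*

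**What the plan says.** In the protocol article, section Analyses, the three primary outcomes are to be compared "on the basis of the 'intention to treat' principle using linear regression models". No model term other than treatment is implied. The section then gives a sequence:

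- A check comes first: "Success of randomisation and normality of outcome measures will be checked before actual analyses are done".
- Adjustment depends on it: "When it turns out that randomisation was (partially) unsuccessful, we will adjust for differences in prognosis".
- Candidates come from the data: "Using baseline characteristics, we can identify factors that influence outcome of the study".
- Selection is numerical: "Factors that change the outcome with 10% will be regarded as confounders and will therefore be added to the regression-model".

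The article gives no criterion for unsuccessful randomisation. It does not say what quantity must change by 10%; the usual meaning is the treatment estimate.

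The section Randomisation describes the allocation: "The randomisation list contains four different strata and is randomised per block of six numbers". The strata are formed "on the basis of the Kellgren-Lawrence score of the hips, knees and hands". Table 2 lists type of OA and radiological severity, the two features behind the strata, under possible confounders or effect modifiers. No section states that the strata or the baseline outcome value are in the primary model. On masking at analysis, "the allocation to treatment A and treatment B will be provided, but not the key to A and B".

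**The concern.** Allocation follows a computer-generated list prepared by an independent researcher, with the key locked away. Under such a scheme baseline differences arise by chance, so a balance check cannot show which model is right. A change-in-estimate rule is meant for confounding in observational data.

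The rule also scales with the result. Ten per cent of an estimate near zero is tiny, so many factors qualify when there is no effect and few qualify when there is one. Adjustment is then least likely when it would help most.

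Stratified blocks balance the stratum factors by design, so these would seldom show imbalance or, at a real effect, move the estimate by 10%. The stated route thus tends to pass over the factors on which the randomisation was built.

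With three primary outcomes the procedure can produce three different models, each known only after outcomes have been examined by group.

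**Working it through.** **Inputs from the protocol article.** Design difference 0.25 mm, SD 0.5, power 80%, alpha 5%, 63 per group, 20% loss to follow-up (Sample size); 222 enrolled (Current status). Standardised effect: 0.25/0.5 = 0.5 SD. Expected completers per arm: 222/2 × 0.8 = 88.8, taken as 88.

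**The plan's own figure.** n = 2(z₁ + z₂)² SD²/d². With two-sided 5%: 2 × (1.960 + 0.842)² × 0.25/0.0625 = 62.8, so 63, as stated. With one-sided 5%, as the text labels it, the result is 50. That mismatch is a separate matter; two-sided 5% is used below.

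**Assumptions not in the article.** Ten independent baseline factors jointly explain 30% of outcome variance. The 10% rule refers to the treatment estimate. Because the trigger is undefined, two readings were simulated: *ungated*, where every factor is tested by the 10% rule, and *gated*, where a factor must first differ between groups at p < 0.05.

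**Step 1: how often the model changes when there is no effect.**
- Ungated: at least one factor enters in 99% of trials, on average 6.2 of 10.
- Gated: at least one enters in about 38–39%, on average 0.5 of 10.

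Ungated, the mean number entered falls to 3.7 at 0.25 SD and 1.2 at 0.5 SD, which shows the dependence on the estimate. Varying the assumption (6 or 10 factors, 20–40% of variance), the share of null trials adding a factor is 98–99.7% ungated and 25–39% gated. At 0.5 SD it is 45–71% and 17–32%.

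**Step 2: validity.** Type I error under the rule is about 4% in the ten-factor setting and 3.3–5.1% across all settings. Bias in the treatment estimate is about 0.01 SD or less.

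**Step 3: power at the design effect (0.5 SD, 88 per arm).**

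| Analysis | Power |
|---|---|
| Unadjusted | about 90% |
| Rule, gated | about 91% |
| Rule, ungated | about 94% |
| All ten factors pre-specified | 97% |

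Check by formula: 0.5 × √(88/2) = 3.317. Unadjusted power is Φ(3.317 − 1.96) = 91%. With all factors in, Φ(3.317/√0.7 − 1.96) = 98%, before the small loss from estimating ten coefficients.

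**Step 4: leaving out the strata.** Suppose the strata are balanced and explain a share R² of variance. The unadjusted standard error is then too large by the factor 1/√(1 − R²), and true size = 2[1 − Φ(1.96/√(1 − R²))].
- R² = 10% (assumed): 1.96/0.949 = 2.066, true size 3.9%.
- R² = 20% (assumed): 1.96/0.894 = 2.191, true size 2.8%.

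Simulation gave 3.6% and 3.2%. At 0.5 SD, simulated power was 91.8% without and 93.2% with strata at R² = 10%, and 93.4% and 95.8% at R² = 20%.

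**Step 5: baseline value as a covariate.** With equal variances at both times and correlation r, the adjusted analysis has (1 − r²)/[2(1 − r)] = (1 + r)/2 of the change-score variance: 0.65 at r = 0.3, 0.85 at r = 0.7, 0.95 at r = 0.9. The article gives no r, so these values are assumptions.

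**The case against.** The strongest reply is that nothing invalid has been shown, and this stands. A reader might infer that picking covariates by their effect on the estimate inflates false positives or makes the confidence intervals misleadingly narrow. The calculations show the opposite: size is at or below 5%, and intervals are slightly wide if the strata matter. Every version also exceeds the planned 80% power at the design effect, because the trial was enlarged to 220. The ungated rule even improves on no adjustment (about 94% against 90%).

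A reader might also take the 99% as the expected behaviour of the plan. It holds only if the 10% rule is run whatever the balance check shows. The text more naturally makes the check a gate, and then the share is well under half.

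Nor does the article exclude the strata or the baseline values. It lists no model terms, it names the stratifying features as possible confounders, and an analysis plan that is not shown might include them. The baseline value already enters through the change outcomes; change score versus baseline adjustment is a matter of efficiency, since both are unbiased under randomisation. Masking of the A/B key also limits deliberate steering towards glucosamine, although the A–B contrast is visible while covariates are chosen.

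What the reply does not meet is the rule itself. The article does not leave covariate choice to another document: it publishes a trigger without a criterion and a numerical rule that refers to the result.

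**Conclusion.** The point holds as a badly fixed rule for the primary model. On either reading of the trigger, which covariates enter depends on chance imbalance, on the observed treatment estimate, or on both, and the model can differ among the three primary outcomes. The only route the article states for the strata or the baseline value is this same rule.

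The consequence is limited: a model that cannot be known in advance, mildly conservative inference if the strata are prognostic, and a loss of roughly 3 to 6 percentage points of power at the design effect (97% against 94% or 91%). These sizes rest on assumed covariate strength, 88 completers per arm and, for the gated reading, an assumed p < 0.05 imbalance criterion. The dependence of the model on the data follows from the text alone. This is a should-fix point, not a must-fix one.

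**What to change.** Before the A/B codes are released, replace the balance trigger and the 10% rule with one fixed linear model for each of JSN, WOMAC pain and WOMAC function. Its terms are treatment, the baseline value of that outcome, the four-level randomisation stratum, and any further baseline prognostic factors named at that time. Keep the baseline comparison as description only, with no role in model choice. Report the unadjusted result as a sensitivity analysis.

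The strata and baseline outcomes are already collected, and the article places all analyses after the end of the trial, so the change is one of wording. It uses about four degrees of freedom (one for the baseline value, three for the strata) among some 176 expected completers. Each further named factor uses at least one more.
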